## Abstract

**Introduction:**

Integration of smoking cessation (SC) into lung cancer screening is essential to optimise clinical and cost effectiveness. The most effective way to use this ‘teachable moment’ is unclear. The Yorkshire Enhanced Stop Smoking study will measure the effectiveness of an SC service integrated within the Yorkshire Lung Screening Trial (YLST) and will test the efficacy of a personalised SC intervention, incorporating incidental findings detected on the low-dose CT scan performed as part of YLST.

**Methods and analysis:**

Unless explicitly declined, all smokers enrolled in YLST will see an SC practitioner at baseline and receive SC support over 4 weeks comprising behavioural support, pharmacotherapy and/or a commercially available e-cigarette. Eligible smokers will be randomised (1:1 in permuted blocks of random size up to size 6) to receive either an enhanced, personalised SC support package, including CT scan images, or continued standard best practice. Anticipated recruitment is 1040 smokers (January 2019–December 2020). The primary objective is to measure 7-day point prevalent carbon monoxide (CO) validated SC after 3 months. Secondary outcomes include CO validated cessation at 4 weeks and 12 months, self-reported continuous cessation at 4 weeks, 3 months and 12 months, attempts to quit smoking and changes in psychological variables, including perceived risk of lung cancer, motivation to quit smoking tobacco, confidence and efficacy beliefs (self and response) at all follow-up points. A process evaluation will explore under which circumstances and on which groups the intervention works best, test intervention fidelity and theory test the mechanisms of intervention impact.

**Ethics and dissemination:**

This study has been approved by the East Midlands-Derby Research Ethics Committee (18/EM/0199) and the Health Research Authority/Health and Care Research Wales. Results will be disseminated through publication in peer-reviewed scientific journals, presentation at conferences and via the YLST website.

**Trial registration numbers:**

ISRCTN63825779, NCT03750110.

Strengths and limitations of this studyThis is the first study to investigate the use of incidental findings as part of a smoking cessation (SC) intervention delivered alongside lung cancer screening, and to evaluate the uptake and effectiveness of a colocated stop smoking service.Recruitment is limited to the number of eligible smokers attending for a lung health check as part of the Yorkshire Lung Screening Trial.SC support will be consistently delivered in line with National Health Service best practice and National Institute for Health and Care Excellence guidance.The scripted approach to explaining lung scan results will support standardisation of intervention delivery.The inclusion of a process evaluation will enhance contextual understanding of study outcomes, including why eligible individuals do not engage with the SC intervention.

## Introduction

Lung cancer is the third most common cancer and has the highest mortality of all cancers in the UK.^1^ It becomes more common as socioeconomic deprivation levels increase,^2^ reflecting higher smoking rates.^3^ A reduction in both all-cause and lung cancer specific mortality was reported by the US National Lung Screening Trial in 2011^4^; subsequently lung cancer screening (LCS) was adopted across North America having been recommended by the US Preventive Services Task Force in 2013.^5^ Mortality benefits of low-dose CT (LDCT) screening for LCS have subsequently been demonstrated by the Multicentric Italian Lung Detection (MILD) trial^6^ and confirmed by preliminary results from the NELSON study.^7^

More than 85% of cases of lung cancer are caused by tobacco smoking,^8^ and stopping smoking at any age significantly reduces lung cancer risk.^9 10^ LCS may provide a teachable moment for smoking cessation (SC);^9^ patients undertaking routine or acute visits to healthcare providers are more likely to be receptive to offers of help to quit.^11^

Several large studies have measured SC outcomes in the context of LCS, with results varying between higher quit rates,^12^ no difference^13^ or lower quit rates in screened versus unscreened participants.^14^ Despite the potential for important health gains, there is limited evidence on how best to integrate effective SC services in an LCS context, though lessons may be learnt from SC interventions delivered in other settings.

Evidence suggests that provision of SC support as an opt-out default generates more quit attempts,^15–17^ and higher uptake within an LCS setting.^18^ A 2014 systematic review showed benefit of materials tailored to the characteristics of individual smokers,^19^ although the included studies were conducted predominantly in the general population, rather than screening participants. Further, a recent UK study has demonstrated the efficacy of including risk information personalised to pre-existing health conditions and consequences of continuing to smoke when inviting participants to SC services.^20^ LDCT screening commonly detects smoking-related comorbidities, a consequence of participants’ long smoking histories.^21 22^ The screening process is a unique opportunity for a personalised SC intervention using these findings to improve quit rates.^23^

The SCALE collaboration in the USA consists of eight ongoing projects, and has recently been established to support projects testing a variety of SC interventions delivered in LCS settings involving LDCT. All share a common core of data collection measures to facilitate data sharing, which will build an evidence base for effective approaches.^24^ One approach not being tested within the SCALE collaboration is the use of incidental scan findings as part of the SC intervention. The Yorkshire Enhanced Stop Smoking (YESS) study intervention consists of a personalised paper-based booklet intervention incorporating images of the heart and lungs from the participant’s own LDCT scan. The booklet will be delivered by an SC practitioner (SCP) specially trained to deliver the intervention components, highlighting the short-term and long- term benefits of cessation while boosting self and response efficacy. To our knowledge, the YESS study is the first to test such an approach.

### Study aims

The primary aims of the study are to:

Assess the uptake and effectiveness of a colocated opt-out SC intervention, delivered in line with National Health Service (NHS) standard best practice (SBP) guidance, as part of an LCS programme.Assess the efficacy of a personalised, theory-grounded SC intervention, incorporating participant heart and lung scan images alongside an explanation of the clinical importance of the findings and scripted communication to enhance personal salience, self-efficacy and response efficacy.

The secondary aims of the study are:

Conduct a process evaluation of both the colocated and personalised SC intervention to support interpretation of study findings.Conduct a health economic evaluation to assess the cost-effectiveness of the colocated service plus personalised feedback intervention over and above the colocated service plus SBP.

## Methods

This protocol is reported in accordance with Standard Protocol Items: Recommendations for Interventional Trials guidance.^25^ Participant flow and study measures are summarised in figure 1.

**Figure 1 F1:**
[figure not shown]
Flow diagram illustrating the path of participants through the study, interventions and evaluations. LDCT, low-dose CT; SCP, smoking cessation practitioner; YLST, Yorkshire Lung Screening Trial; SSS, stop smoking service

### Trial design

This is a pragmatic, parallel-group, open, randomised controlled trial comparing an enhanced, personalised SC support package, tailored to include results from LCS, delivered in addition to an SBP cessation package, versus SBP package alone. Further, we will also compare the effectiveness of the colocated service with local stop smoking services (SSS) in an observational design.

### Participants and recruitment

Participants included in the YESS study will have been invited to attend a lung health check (LHC) (including LDCT screening for lung cancer) as part of the Yorkshire Lung Screening Trial (YLST) (funded by Yorkshire Cancer Research, award reference L403, 2016 round REC reference 18/NW/0012).^26^ In brief, participants are aged 55–80, registered with a general practitioner (GP) in the Leeds Clinical Commissioning Group area and registered as a current or ex-smoker in primary care databases. Participants will be considered eligible for LDCT screening if they meet the criteria of either USPSTF,^27^ PLCO_M2012_
28 or LLP (v2)^29^ models.

### Inclusion criteria

All individuals who attended an LHC and consent to participate in the YLST, have smoked within the last month or have an exhaled carbon monoxide (CO) reading ≥6 ppm and have agreed to see an SCP on the mobile unit.

### Exclusion criteria

Any individual who does not have an LDCT scan, or is unable to provide informed consent.

### Participant withdrawal

Participants may be withdrawn from the trial either at their own request or at the discretion of the Investigator. Participants will be made aware that this will not affect their future care.

### Randomisation

After the screening visit, but before the 4-week follow-up, all smokers who agreed to see the SCP will be randomised to either continued SBP or intervention using concealed allocation. The randomisation sequence (1:1 in permuted blocks of random size up to size 6) will be generated using a computer random-number generator and participants allocated sequentially, overseen by the University of Nottingham clinical trials unit.

### Blinding

The sequence of treatment allocations will be concealed until interventions have all been assigned and recruitment and data collection are complete. Once primary and secondary data from both treatment groups have been analysed by the trial statistician, the groups will be un-blinded to the Trial Management Group (TMG). Consent is taken at the 4-week visit by the SCP. In order to ensure concealment at the time of recruitment/consent, the personalised risk information booklet (further detail provided later) or a blank booklet are enclosed in a sealed envelope which is opened by the SCP following consent/data collection. This arrangement commenced five rounds into recruitment following review of processes at a Trial Steering Committee. For five rounds at the start of the trial, SCPs were aware of trial allocation at the time of consent/data collection. The impact of this will be assessed in a sensitivity analysis.

### Sample size

Recruitment will be limited to the number of eligible smokers attending for an LHC over the 2-year YLST recruitment period. Based on early recruitment figures, we anticipate 1040 smokers enrolling in YESS.

Those in the SBP group will be provided with a service similar to that provided by national NHS SSS. A 2010 systematic review of relapse rates among smokers quitting with national NHS SSS found that 53% had quit at 1 month, and 15% at 1 year.^30^ Fitting an exponential decay function to these figures we estimate a monthly relapse rate, after 1 month, of 11.5%. Applying these figures to our study design we would expect a quit rate of 41% at 3 months in those receiving SBP. If the cessation rate is 41% in the usual care group, a study of 1040 individuals will provide 90% power to detect an increase to 51% (ie, an increase of 10%), and 80% power to detect an increase to 49.6% (ie, an increase of 8.6%).

### Study duration

Participants will be recruited to YESS between January 2019 and December 2020 with follow-up data collection ending December 2021. Stop smoking support will be provided for as long as the participant requires, up to 12 weeks. Follow-up contact will be requested at 4 weeks, 3 months and 12 months, with a 2-week window to accommodate participant availability. The latter will also apply to interviews conducted for the process evaluation.

### SC provision

#### All eligible smokers

Unless explicitly declined, all eligible YLST participants will attend a consultation with a specialist SCP, trained to National Centre for Smoking Cessation and Training standards,^31^ colocated within the screening van. Support will be provided in line with National Institute for Health and Care Excellence (NICE) PH48 guidance^32^ comprising one session of behavioural support at the time of the LHC and provision of pharmacotherapy (either as nicotine replacement therapy through delegated prescribing at the visit and/or a commercially available e-cigarette, or arrange a GP prescription for varenicline or bupropion). Follow-up contact either face-to-face or by telephone, typically weekly but more or less frequently according to participant preference for up to 4 weeks from the date of the LHC.

Where study SCP follow-up is not possible, or if the individual smoker prefers, contact details will be passed to the local NHSSSS for referral into community services immediately following the screening visit.

All eligible participants will be asked for consent to be contacted by telephone at 4 weeks, 3 months and 12 months after the screening visit solely to ascertain smoking status, with optional CO validation if quit. Approximately 4 weeks after the screening visit (and hence after scan results have been issued by YLST), the SCP will arrange a face-to-face visit with the smoker either at home or community location (according to the participant’s preference) to ascertain current smoking status (with CO validation in those reporting abstinence). Informed written consent for participation in the trial will be confirmed at this visit, and individuals treated according to their allocated group as follows:

#### SBP group

Pharmacotherapy/e-cigarettes and behavioural support will continue to be offered and arranged, as outlined above.

#### Intervention

##### Personalised booklet with LDCT scan images

In addition to SBP and YLST standard feedback, participants are provided with information about their scan findings in a personalised booklet. Where the reporting radiologist has identified emphysema or coronary artery calcification (CAC), a trained research radiographer will select appropriate images for use in the booklet. All images are accompanied by brief text to provide context and explanation.

Where the participant’s scan shows emphysema, an axial image displayed using lung windows that best demonstrates this will be extracted, and a red outline drawn around the emphysematous area to highlight this finding. Where possible, an image from another part of the participant’s scan showing normal lung parenchyma will be shown alongside the emphysematous image to highlight that there are areas of healthy lung than can be protected by SC. Where emphysema is present throughout both lungs, an image will be selected showing an area of relative sparing. Where emphysema is not present at all, an image of the participant’s normal lung will be shown alongside a library scan image of severe emphysema. An artists’ impression of a lung, showing healthy and damaged emphysematous areas will be included to aid participant comprehension (see figure 2A–C, for examples).

**Figure 2 F2:**
[figure not shown]
Example of a booklet page for (A) participant with no visible emphysema; (B) participant with ‘moderate’ emphysema; (C) participant with ‘severe’ emphysema; (D) participant with no visible coronary artery calcification (CAC); (E) participant with CAC.

Where CAC is present, the axial image displayed using mediastinal windows that best demonstrates this will be extracted and shown alongside an artist’s impression of the heart, with the corresponding area of calcification annotated with yellow shading. Where CAC is not present, the participants’ own normal scan image will be shown alongside an artist’s impression of the heart demonstrating what might happen were the participant to continue smoking. In all cases, an additional artist’s impression of health and narrowed coronary arteries are shown (see figure 2D, E, for examples). Five per cent of all booklets produced will be audited by a respiratory physician or radiologist to ensure that appropriate images, annotations and text are used in the resource.

The booklet will also contain generic short-term and longer-term benefits of quitting derived from the Smokefree NHS website^33^ and contact details for the YESS study project manager, the local NHSSSS, the YLST clinical team and the assigned SCP.

##### Scripted communication to explain clinical importance and target behavioural components

The SCP will explain the biological nature of emphysema and CAC and will provide feedback and further SC advice tailored to the result. The SCP will highlight specific benefits to risks of lung cancer, Chronic Obstructive Pulmonary Disease (COPD) or cardiovascular disease arising from quitting including the reduced progression of existing emphysema or smoking-damage. SCP’s communication about the personalised risk booklet is supported by scripts which exemplify how each section should be communicated in each of the different result scenarios. The scripts model communication techniques and language designed to target the behavioural intervention components; specifically, to increase personal salience, self-efficacy and response-efficacy, while mitigating the potential for anxiety and over-reassurance. They use lay language to illustrate the steps of disease progression and emphasise the short-term and immediate benefits of quitting for participants’ health. This scripted approach also aims to help standardise intervention delivery. Where required, participants are offered the opportunity for a telephone consultation with a respiratory physician to discuss scan findings.

### Data collection

Data collection measures are summarised in table 1.

**Table 1 T1:** Data collection measures in study participants

	Baseline	4 weeks	3 months	12 months
Smoking behaviour (including CO validation if abstinence is reported)	X	X	X	X
Motivation to quit smoking	X	X	X	X
Quit confidence	X	X	X	X
Self-efficacy of quitting smoking	X	X	X	X
Use of smoking cessation support	X			X
Wider healthcare resource use	X		X	X
Response efficacy of quitting smoking		X	X	X
Perceived risk of cancer developing cancer		X	X	X
Cancer worry score		X	X	X
Quality of life (EQ-5D-5L)	X		X	X

CO, carbon monoxide.

### Outcome measures

#### Primary outcome

Seven day point prevalent CO validated SC 3 months after the LHC in all participants enrolled in the YESS study.

#### Secondary outcomes

Self-reported and CO validated continuous cessation at 4 weeks in all eligible smokers agreeing to receive SC from the SCP as part of the LHC.Self-reported continuous and seven day point prevalent SC at 3 months.Self-reported and CO validated continuous cessation at 12 months.Attempts to quit smoking.Changes in psychological variables, including perceived risk of lung cancer, motivation to quit smoking tobacco, confidence and efficacy beliefs (self and response) at all follow-up points.

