### Statistical analyses

We will compare baseline characteristics between randomised treatment groups descriptively. We will estimate the effect of the intervention by comparing our primary and secondary outcomes between intervention and SBP groups using logistic regression, presenting results in terms of the proportion achieving abstinence in the two groups, the risk difference and the OR, with 95% CIs.

Primary analysis will be on an intention to treat basis, assuming that missing data implies smoking, but we will conduct sensitivity analysis to examine the impact on our findings of alternative assumptions, including the Hedeker approach which assumes alternative relationships between having missing data and smoking, and using multiple imputation to test the alternative assumption that the data are missing at random (ie, missing data can be modelled using measured variables).

We do not plan a priori to adjust for any baseline covariate, presuming that randomisation will achieve balance between groups. We will look for effect modification of effect of intervention according to presence of absence of abnormal scan findings of emphysema or CAC, using the likelihood ratio test for interaction. In sensitivity analysis, we will analyse excluding those who were consented to the intervention group prior to change in timing of consent (n=94).

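### Change in perceived risk and response efficacy is defined at every follow-up point, but neither is measured before 4 weeks, so their 4-week change and any change from the lung health check cannot be computed

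*Protocol article*

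**What the plan says.** All references are to the protocol article.

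- **Secondary outcomes** names changes in five psychological variables: perceived risk of lung cancer, motivation to quit, and "confidence and efficacy beliefs (self and response) at all follow-up points".
- **Study duration** fixes those points: "Follow-up contact will be requested at 4 weeks, 3 months and 12 months".
- **Data collection, Table 1** marks the rows "Response efficacy of quitting smoking" and "Perceived risk of cancer developing cancer" at 4 weeks, 3 months and 12 months, with the baseline cell empty. The row "Self-efficacy of quitting smoking" is marked at baseline and at all three follow-ups, as are motivation and quit confidence.
- **Blinding** describes the 4-week visit. The personalised or blank booklet is "enclosed in a sealed envelope which is opened by the SCP following consent/data collection". This began after five recruitment rounds; before that, practitioners knew the allocation when they took consent and collected data.
- **SC provision, All eligible smokers** places the 4-week visit after the scan results have been sent out, with cessation support offered from the lung health check onwards. Allocated treatment follows consent at that visit.
- **Statistical analyses** describes "comparing our primary and secondary outcomes between intervention and SBP groups using logistic regression", with abstinence proportions, risk difference and odds ratio as summaries. It plans no baseline covariate adjustment and names no separate method for the psychological variables.

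**The concern.** A change needs two measurements. For two of the five named variables the first measurement is at 4 weeks, which is also the first point at which a change is promised. The outcome definition and the measurement schedule therefore conflict, and no later analysis document can supply a value that was not collected.

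The 4-week point has a second difficulty. Where the envelope is opened after data collection, both arms have been treated alike when the 4-week scores are taken. An arm comparison at that point tests a booklet that nobody has yet seen.

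The stated model is a third, lesser matter. Logistic regression needs a binary outcome, and a change in a graded score is not one unless a cut-point is set. None is given.

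What is at stake is the test of mechanism. Raising self-efficacy and response efficacy is a declared purpose of the scripted communication, and the process evaluation is meant to test how the intervention works. If the reference time is not fixed in advance, the analyst chooses it later.

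**Working it through.** **Plan's own figures.** The article gives none for the psychological outcomes. Its only power statement concerns the primary outcome, and it reproduces. Assume two-sided 5%, n = 520 per arm and no continuity correction, with power = Φ{[√n·|p2 − p1| − 1.96·√(2p̄(1 − p̄))] / √(p1q1 + p2q2)}, where q = 1 − p and p̄ is the mean of p1 and p2.

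- 41% v 51%: (2.280 − 1.381)/0.701 = 1.282, power 90.0%.
- 41% v 49.6%: (1.961 − 1.380)/0.701 = 0.829, power 79.6%.

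Neither figure depends on the point below.

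**Schedule against definition.** The inputs are the marks in Table 1 and the three follow-up points in Study duration. I take the perceived-risk row of Table 1 to be the measure named in Secondary outcomes.

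| Variable | Baseline | 4 wk | 3 mo | 12 mo | Change from baseline | Change from 4 wk |
|---|---|---|---|---|---|---|
| Motivation | X | X | X | X | 3 of 3 points | 2 of 3 |
| Confidence | X | X | X | X | 3 of 3 | 2 of 3 |
| Self-efficacy | X | X | X | X | 3 of 3 | 2 of 3 |
| Response efficacy | – | X | X | X | 0 of 3 | 2 of 3 (3 and 12 mo) |
| Perceived risk | – | X | X | X | 0 of 3 | 2 of 3 (3 and 12 mo) |

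For the last two rows, no choice of reference gives a change at all three points.

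**Order of events.** In the sealed-envelope rounds the sequence is: lung health check and support, scan results, 4-week consent and data collection, envelope opened, booklet. The 4-week score is thus pre-intervention and can serve as a reference. It is not a pre-screening score.

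**Precision of the alternatives.** Let r be the correlation between the 4-week and later score, with equal variances at the two times (both assumed; the article gives neither). Relative to an unadjusted comparison of the later scores:

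- variance adjusted for the 4-week score = 1 − r²;
- variance of the raw change score = 2(1 − r).

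| Assumed r | Adjusted | Raw change |
|---|---|---|
| 0.3 | 1 − 0.09 = 0.91 | 2 × 0.7 = 1.40 |
| 0.5 | 1 − 0.25 = 0.75 | 2 × 0.5 = 1.00 |
| 0.7 | 1 − 0.49 = 0.51 | 2 × 0.3 = 0.60 |

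Adjustment cuts the variance by 9%, 25% and 49%. A raw change score loses precision at r = 0.3, breaks even at 0.5, and at 0.7 gains less than adjustment does.

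**The case against.** The strongest reply has four parts.

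1. *The outcomes can still be analysed.* Change from 4 weeks to 3 and 12 months is available, and a randomised comparison of levels at those times needs no baseline at all. This stands. A reader might infer that the mechanism outcomes cannot be computed; the schedule does not support that. Only change at 4 weeks and change from the lung health check are lost.
2. *The logistic sentence is about cessation.* Its summaries are abstinence proportions, and the article promises a detailed SAP. This largely stands. The response formats are not given either, so it is an inference from the word change that these are graded scores. A reader might go on to price a loss from dichotomising: a median split of a normal score keeps 2/π = 0.64 of the information, a loss of about 36%. No such split is planned, so that figure measures nothing in this document.
3. *Different reference times do no harm.* Each scale is compared between arms separately, and any score taken before the booklet is a valid reference. This stands. Motivation, confidence and self-efficacy have no schedule defect and need not change.
4. *The 4-week score is imperfect.* It follows the scan results and about four weeks of support, and in the first five rounds it was collected by practitioners who knew the allocation. Adjusting for it also departs from the stated no-covariate plan. These points stand as conditions on the fix, not as reasons to leave the conflict.

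Cancer worry shares the missing baseline in Table 1, but Secondary outcomes does not name it, so it is not part of this point.

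**Conclusion.** The conflict is real and limited. For two of the five named variables, one of the three promised time points has no computable change under any reference, and change from the lung health check exists at none. This follows from the article alone and needs no assumption beyond matching the perceived-risk row to the named outcome.

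That a 4-week arm comparison is uninformative about the booklet follows from the sealed-envelope sequence, and is documented only for the rounds that used it. The model mismatch holds on a literal reading only, and the unseen SAP may already resolve it.

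The gain from adjusting for the 4-week score cannot be fixed from the document: it is r², or 9% to 49% of the variance over assumed r of 0.3 to 0.7. The primary outcome, the sample size and the main conclusion on cessation are not touched. It should be corrected because the correction needs no new data and settles the reference time in advance.

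**What to change.** 1. For perceived risk and response efficacy, define the outcome as the score at 3 and at 12 months, with the 4-week pre-booklet score as reference. Drop 4 weeks as an outcome time for the arm comparison; it can be reported descriptively.
2. Let motivation, confidence and self-efficacy keep the lung health check baseline, or use the 4-week score as well; state which.
3. Limit the logistic model to binary outcomes. Compare the psychological scores by linear or ordinal regression, according to response format, adjusted for the pre-intervention score. Report the adjusted difference (or the ordinal odds ratio) with a 95% CI, and state this as an exception to the no-covariate plan.
4. Repeat the analysis without participants from the first five rounds, when practitioners knew the allocation at data collection.

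Cost: a few lines in the outcome definitions and the SAP, and one extra sensitivity run. No new measurement is needed, because the 4-week scores are already scheduled.
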